### Safety assessment protocol

2.9

The safety assessment protocol includes the registration of all the adverse events that may arise during the clinical trial. Additionally, vital signs, physical examinations, and monitoring of concomitant medications will be performed to assess the safety.

#### Treatment emergent adverse events assess

2.9.1

Treatment-emergent adverse events (TEAE) will be assessed from the initial application of the trial until its end. In this study, TEAE means an adverse event that occurred after the application of an investigational device, that is after tDCS application. TEAE events related to tDCS will be identified during and up to 30 min after each tDCS application.

All TEAE will be standardized using System Organ Class (SOC) and Preferred Term (PT) in the most recent version of the Medical Dictionary for Regulatory Activities (MedDRA). If the same TEAE occurs multiple times in one person, it will be classified as a single case; however, if the severity of the same TEAE varies, only the maximum severity TEAE will be recorded. If the causality of the same adverse event differs for the same person, only the adverse events that appear to be caused by tDCS will be recorded. The number of subjects with TEAEs, number of events and percentage per events will be registered and organized into adverse device events (ADEs), serious adverse events (SAEs), and serious adverse device events (SADEs).

Additionally, the differences between groups will be tested using the Pearson’s chi-square test (or Fisher’s exact test if the expected frequency is less than five cells and exceeds 20%). After standardizing the latest version of the MedDRA code, SOC, and PT, TEAE’s occurrences will be reported for each group.

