### Recruitment and study setting

2.2

The study is expected to take place in the following hospitals: the Catholic University of Korea, Yeouido St. Mary’s Hospital (Seoul, Republic of Korea); the Catholic University of Korea, Seoul St. Mary’s Hospital (Seoul, Republic of Korea); and the Catholic University of Korea, St. Vincent’s Hospital (Suwon, Republic of Korea). Each hospital will screen and recruit volunteers who meet all the inclusion criteria and none of the exclusion criteria below (See Table 1).

**Table 1 tab1:** Schedule of enrollment, interventions, and assessments.

Schedule	Screening	Baseline	tDCS intervention: Set 1		Resting period	tDCS intervention: Set 2	
			3 weeks: 15 sessions	First Post-test		3 weeks: 15 sessions	Second Post-test
Visit	V1	V2	V2–V16	V16	Minimum 2 weeks ±7 days	V17–V31	V31
ENROLLMENT							
Informed consent	V						
Assigning Screening Numbers	V						
Demographic Survey	V						
Medical/surgical history	V						
Evaluation of inclusion/exclusion criteria	V	V					
Vital signs	V		V			V	
Anthropometry and physical examination	V	V	V			V	
Pregnancy test	V						
Laboratory tests	V						V
Prior/Concomitant Medications	V		V			V	
MRI scan	V						V
Randomization		V					
INTERVENTION							
Medical device preparation		V					
tDCS application			V			V	
ASSESSMENTS							
ADAS-Cog	V			V			V
K-MMSE	V			V			V
MoCA-K	V			V			V
HAM-D	V			V			V
S-IADL	V			V			V
Cortical Electric Field Assessment		V					
Adverse events scan			V			V	

tDCS, transcranial direct current stimulation; V, visit; MRI, magnetic resonance imaging; ADAs-Cog, Alzheimer’s disease assessment scale-cognitive subscale; K-MMSE, Korean version of Mini-Mental State Examination; MoCA-K, Korean version of Montreal Cognitive Assessment; HAM-D, Hamilton Depression Rating Scale; S-IADL, Seoul Instrumental Activities of Daily Living.

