According to a previous study, five consecutive sessions of tDCS in patients with MCI at 2 mA for 20 min over F3 significantly improved delayed recall, with results persisting after one month of follow-up (48). Another study applied tDCS in patients with AD for 25 min daily (10 sessions) at 2 mA to determine its effectiveness in treating cognitive decline, and found that the MMSE scores showed significant changes that were maintained at 1 and 2 months after the intervention (49). According to previous research, the effects of tDCS can be maintained for at least one month after five sessions, which shows that a resting period of two weeks is sufficient without diminishing the effectiveness of tDCS.

To the best of our knowledge, personalized bilateral optimization of tDCS in patients with AD-induced MCI has not been reported. Nevertheless, a similar study applied six sessions of personalized optimized anodal high-definition tDCS at 2 mA for 20 min to adults with AD, which resulted in significant improvement of the MMSE scores in comparison with the sham group (16). However, we believe that the validity of bilateral tDCS with two electrodes still needs to be validated and this trial aims to validate the safety and efficacy of personalized tDCS as a new tDCS protocol.

The trial presents various limitations. First, the absence of a group using conventional tDCS electrode locations guided by the 10–20 EEG-based system for comparison between optimized and conventional tDCS electrode locations. After concluding this trial, we will consider including a conventional tDCS group in future studies. Second, no previous studies have directly supported the safety of the electrode type chosen in this study. Nevertheless, this study will be able to validate its efficacy and safety relative to sham tDCS. Third, the absence of a follow-up evaluation to determine if the effectiveness of the treatment will be maintained in time. A follow-up evaluation will be considered in future fully powered trials.

For this present study, we hypothesize that the participants will tolerate the optimized tDCS intervention without any significant adverse effects, and that, compared to the sham tDCS group, the optimized personalized tDCS application will affect the treatment of patients with MCI-induced AD for cognitive function.

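### The 30-minute window for identifying device-related adverse events conflicts with the whole-trial TEAE period, and the single-case rule conflicts with the promised event count

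*Protocol article*

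**What the plan says.** Section 2.9 of the protocol article opens broadly: "The safety assessment protocol includes the registration of all the adverse events that may arise during the clinical trial". Section 2.9.1 keeps that scope for TEAEs: "Treatment-emergent adverse events (TEAE) will be assessed from the initial application of the trial until its end". Its definition sets no limit on onset: "TEAE means an adverse event that occurred after the application of an investigational device, that is after tDCS application". The next sentence gives a much narrower rule for the device-related subset: "TEAE events related to tDCS will be identified during and up to 30 min after each tDCS application".

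The same section then sets the counting rules. "If the same TEAE occurs multiple times in one person, it will be classified as a single case", only the worst grade is recorded when severity varies, and the device-related occurrence is kept when causality varies. It goes on: "The number of subjects with TEAEs, number of events and percentage per events will be registered", with results sorted into adverse device events (ADEs), serious adverse events (SAEs) and serious adverse device events (SADEs).

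In Table 1 (section 2.2) the row "Adverse events scan" is marked under the two session blocks, V2–V16 and V17–V31, and not under the resting period. Safety is the second specific aim in the Introduction, and the Discussion concedes that "no previous studies have directly supported the safety of the electrode type chosen in this study".

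**The concern.** Two pairs of statements in section 2.9.1 do not fit together.

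- **Period.** TEAEs run to the end of the trial, but the one sentence on how device-related TEAEs are identified ties them to the session and the half hour after it. Site staff could reasonably take this as a cut-off. A skin reaction or headache that begins the same evening would then be a TEAE but not an ADE.
- **Counting.** If repeats are a single case and only the worst grade is recorded, the data may not contain what is needed for the promised number of events.

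The ADE and SADE counts are the figures that answer the safety aim. Section 2.4.4 gives the sham arm only brief current ramps, so late reactions truly caused by stimulation would be expected mainly in the active arm. Leaving them out of the device-related counts would make the arms look more alike than they are. Repeated mild reactions also matter: section 4 gives the unreported safety of this electrode size in MCI as the reason for dividing the 30 sessions into two blocks.

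**Working it through.** **The plan's own figure.** Section 2.9 gives no number to reproduce. The one reproducible sample-size figure, in section 2.7, is 32/(1 − 0.20) = 40. It is correct and not in dispute. With 1:1 allocation (section 2.3.4) it gives 20 per arm, used below.

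**Size of the window.** Inputs: 30 sessions (section 2.1), 30 min of stimulation (section 2.4.1), 30 min afterwards (section 2.9.1), two 3-week sets (section 2.1), and a rest of 2 weeks ± 7 days (Table 1).

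- Window: 30 × (0.5 h + 0.5 h) = 30 h.
- Total with a 2-week rest: (3 + 2 + 3) × 7 × 24 = 1,344 h; 30/1,344 = 2.2%.
- With a 1-week rest: 7 × 7 × 24 = 1,176 h; 30/1,176 = 2.6%.
- With a 3-week rest: 9 × 7 × 24 = 1,512 h; 30/1,512 = 2.0%.

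This measures how far the two stated periods differ. It does not estimate the proportion of events affected, because the documents give no distribution of onset times.

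**What happens to a late reaction.** Take a reaction that starts six hours after a session.

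1. Section 2.9 registers it as an adverse event.
2. The definition in section 2.9.1 makes it a TEAE.
3. The 30-minute sentence does not cover it, and no other sentence says how it would be identified as related to tDCS.
4. Its entry into the ADE or SADE count is therefore undetermined.

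**Effect of collapsing repeats.** The documents give no event rates. Assume a per-session probability p of a given reaction, independent across sessions, with 20 participants in an arm. Expected occurrences are 20 × 30 × p; expected cases after collapsing are 20 × (1 − (1 − p)^30).

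| p (assumed) | Occurrences | Cases after collapsing | Cases / occurrences |
|---|---|---|---|
| 0.02 | 12 | 9.1 | 0.76 |
| 0.05 | 30 | 15.7 | 0.52 |
| 0.10 | 60 | 19.2 | 0.32 |
| 0.20 | 120 | 20.0 | 0.17 |

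If one arm had p = 0.20 and the other p = 0.10, occurrences would be 120 against 60, a twofold difference. The share of participants affected would be 1 − 0.80^30 = 99.9% against 1 − 0.90^30 = 95.8%. Participant incidence is correct in both arms but hardly separates them; the event count would show the difference.

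**The case against.** The 30-minute sentence does not contain the word only. It can be read as a scheduled observation period added to general registration, and sections 2.9 and 2.9.1 would still register a later event. The rule for differing causality rests on what appears to be caused by tDCS, states no onset limit, and keeps the related occurrence. Visits take place five times a week within each set, and section 2.9.3 adds a review at each visit partly to identify adverse events. All of this stands. It means that a reader who inferred systematic loss of events would go beyond the text: the doubt concerns attribution to the device, not registration.

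A reader might also infer from Table 1 that the post-tests go unscanned. They do not. They fall on V16 and V31, inside the marked session blocks. V17, the first visit after the rest, is also inside a marked block, and no visit is scheduled during the rest.

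Counting a person once per term at worst severity is the usual convention for incidence tables and removes no affected person. That stands too. What remains is that the section words the rule as one of recording and then promises event counts, without saying that repeats are kept.

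Finally, a reader might object to the chi-square or Fisher comparison of arms. The section adds it to the counts and percentages. How such tests are presented, and whether intervals go beside them, is commonly left to the analysis plan, so it is no part of this point.

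**Conclusion.** The point holds as an internal conflict that should be resolved. Section 2.9.1 states a 30-minute rule for device-related TEAEs beside a TEAE period with no onset limit: about 30 h against roughly 1,344 h per participant, or 2.0% to 2.6% of clock time over the stated range of the rest period. Followed literally, the rule could make ADE and SADE counts too low, mainly in the active arm. By how much cannot be said, since it depends on how sites read the sentence and on how many reactions start late, and the documents settle neither.

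The single-case rule conflicts with the promised number of events. Participant incidence is unaffected, but recurrence over 30 sessions may be lost. Under the assumed per-session rates of 0.02 to 0.20, collapsed cases would be 76% down to 17% of occurrences; those rates and their independence across sessions are illustrative.

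The documents do not support a claim that adverse events go unregistered, or that the safety comparison is already biased.

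**What to change.** - In section 2.9.1, state that the 30 minutes is the scheduled post-session observation and not a limit on relatedness, and that the relatedness of every TEAE is assessed whenever it starts.
- Word the adverse event scan already marked for the session visits so that it asks about the time since the last session, and at V17 about the whole rest period.
- Record every occurrence with its date and severity. Apply the single-case, maximum-severity rule only to participant-incidence tables, and take event counts from all occurrences.

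The cost is protocol and case record form wording plus a few minutes at visits that already take place. The downside is small: more mild events will be recorded.

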Research has shown that tDCS improves the cognitive state of patients with MCI when applied at an intensity of 2 mA for either 20- or 30 min over periods of 10–20 days (5, 11, 12), showing the potential of tDCS to be used during long-term interventions. According to previous research, tDCS has also demonstrated positive outcomes during long-term interventions for patients with disorders such as depression. In a study involving individuals with major depressive disorder, 15 sessions of anodal tDCS were initially administered, with participants having the option to continue for an additional 15 sessions. The results indicated that those who extended the intervention experienced more lasting benefits than those who completed the intervention after the initial 15 sessions (13). While the past study focused on a different population, it highlights the significance of prolonged tDCS interventions. Hence, assessing the safety and feasibility of tDCS for at least 30 days in patients with MCI is necessary for broader future applications.

Moreover, the effects of tDCS depend not only on the stimulation parameters, but also on distinct individual brain characteristics. A study that included participants with MCI and major neurocognitive disorders applied tDCS at 2 mA for 20 min twice a day for 5 consecutive days but found no significant improvement in cognitive function as assessed through the Mini-Mental State Examination (MMSE) and Alzheimer’s dementia assessment scale–cognitive subscale (ADAS-Cog). According to the authors, the results may have been influenced by various factors, such as a small sample size and the target population, including participants in different stages of neurocognitive impairment (14).

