### Trial design

2.1

The trial design is a prospective, multicenter, double-blind, randomized, active/sham group feasibility study. The active control group named the optimized-tDCS group will be compared with the sham-tDCS group to determine the feasibility and safety of optimized tDCS in the treatment of patients with MCI induced by AD. The intervention will be divided into two sets of 15 sessions (five times per week for 3 weeks), with a resting period of a minimum of 2 weeks between sets. In total, the participants will undergo 30 sessions of Active or Sham tDCS (Figure 1).

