#### Randomization

2.3.4

The participants will be randomized to the Optimized-tDCS and Sham-tDCS groups using a 1:1 ratio following the order of registration by a statistician who will not be involved in the application of the clinical trial. A stratified blocked randomization method with prespecified block sizes will be used. The stratification factor will be the hospital from which participants will be recruited. Random allocation numbers will be sealed in an opaque envelope and delivered to the medical device investigator who will administer the tDCS device in the hospital and will not be involved during the outcome measurement periods or other periods of the research.

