### Sample size

2.7

A prospective sample calculation was not performed because the current study protocol is for assessing feasibility, safety, and trends in effectiveness, which will be utilized to generate data for future full-scale randomized controlled trials. However, as sample sizes of a minimum of 24 participants (12 per group) were recommended, we decided to recruit a minimum of 32 participants based on the predicted recruitment rates within the study timeframe (38, 39). Considering a 20% dropout rate, the projected number of participants to be recruited will be 40.

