In addition, recent research has found that age and biological sex influence the current density at a target point. A study using 3D modeling based on approximately 700 individuals’ MRIs determined that older female adults received a higher simulated current at the DLPFC target area than their counterparts using the same tDCS protocol. They concluded that individual modeling is required to account for the variability in cortical morphometry and to adjust the stimulation parameters of tDCS to achieve the intended stimulation benefits (45).

Moreover, the effect of tDCS is influenced by electrode characteristics (46). Generally, most tDCS studies have used electrode sizes of 25 cm^2^ to 35 cm^2^ with currents between 1 and 3 mA and a duration of 20–30 min. Large electrodes stimulate large regions of the brain and computer simulation studies have shown no focal current density distribution. In addition, these electrodes contribute to the edge effect, which is the current concentration at the edges of the electrodes at the corners of the rectangular and square electrodes. Using smaller and circular electrodes may help decrease edge effects and improve the focus of the current in the target area (46). Therefore, 1.5 cm disk electrodes will be employed in this study.

The use of tDCS for 20 days in patients with MCI has been proven to be safe (5). Moreover, one study safely applied tDCS for six months in patients with AD at an intensity of 2 mA for 30 min (41). However, these previous studies used wider electrodes (rectangular 7 × 5 cm and round 6 cm diameter, respectively) than those used in the present study. In a study with healthy volunteers, one session of 1 mA for 12 min was applied using electrodes (3.14 cm^2^) to the sensorimotor area without reporting adverse effects; to the best of our knowledge, this is the only study that used two electrodes of a similar small size to ours (47). Our study will use small disk electrodes for a relatively long period (30 sessions in total); therefore, as the safety of this electrode size in an MCI population has not yet been reported, the decision to divide the 30 sessions into two blocks of 15 sessions with a resting period in between was made.

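### The planned adverse-event summary pools both stimulation sets, so it cannot show whether harm fades after set 1 or recurs, worsens or first appears in set 2

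*Protocol article*

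**What the plan says.** Safety is the second of the three specific aims. The Introduction argues that "assessing the safety and feasibility of tDCS for at least 30 days in patients with MCI is necessary for broader future applications". The Discussion links the shape of the exposure to a gap in safety knowledge. Because nothing has been published on how safe electrodes this small are for patients with mild cognitive impairment, it explains, "the decision to divide the 30 sessions into two blocks of 15 sessions with a resting period in between was made". The design is two sets of 15 sessions, 30 in all, with at least two weeks of rest between them (section 2.1).

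Section 2.9.1 fixes how TEAEs are handled:

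- There is one observation window, from the first application to the end of the trial.
- The same TEAE occurring more than once in a person is a single case.
- If its severity varies, only the worst grade is recorded.
- On the summary measure: "The number of subjects with TEAEs, number of events and percentage per events will be registered". Results are grouped as adverse device events (ADEs), serious adverse events and serious adverse device events.
- Arms are compared by a chi-square or Fisher test, and occurrences are reported per arm.

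Neither set of onset nor number of sessions received enters any of these rules, and no denominator is stated. On collection, Table 1 marks an adverse-event scan under both sets, and section 2.9.1 has device-related TEAEs identified during each session and for 30 minutes afterwards.

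**The concern.** The trial was given two blocks for a safety reason, so the natural safety question is how a second block is tolerated after a first. The summary in section 2.9.1 does not address it. The gap goes beyond a missing table, because the printed rules themselves remove the relevant signal. A scalp reaction seen in set 1 that returns in set 2 is one case. One that goes from mild to moderate on re-exposure is one moderate case with no set attached.

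A second, smaller issue is the denominator. If everyone randomized is counted, people who left before set 2 are included in a percentage that readers will take as describing 30 sessions.

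The trial is meant to inform a fully powered one. A low pooled percentage could be carried forward as evidence on 30 sessions without anyone having looked at the second set separately.

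**Working it through.** **1. Inputs.** Section 2.7: "we decided to recruit a minimum of 32 participants", and "Considering a 20% dropout rate, the projected number of participants to be recruited will be 40". Section 2.3.4: allocation "using a 1:1 ratio following the order of registration". The article gives no TEAE rate, no timing of dropout and no target precision for safety, so the risks and timing below are assumptions.

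**2. The plan's own figure.** 32 / (1 − 0.20) = 40, which reproduces exactly. At 1:1 this is 20 per arm starting and 16 per arm remaining after the planned loss.

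**3. Can the pooled percentage separate rising from falling harm?** Let p1 and p2 be the risks of a first event in set 1 and set 2, and d the share stopping between sets. Then

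whole-trial risk = p1 + (1 − d)(1 − p1) p2.

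With d = 0.20:

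| Pattern | p1 | p2 | Whole-trial risk |
|---|---|---|---|
| Falling | 40% | 10% | 0.40 + 0.8 × 0.6 × 0.10 = 44.8% |
| Rising | 10% | 48.3% | 0.10 + 0.8 × 0.9 × 0.483 = 44.8% |

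The result does not depend on dropout. With d = 0, 40% then 10% gives 46%, and so does 10% then 40%.

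**4. The once-per-person rule, in counts.** Two illustrative active arms, with 20 starting and 16 entering set 2:

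- Arm A: 6/20 have the event in set 1 and 0/16 in set 2.
- Arm B: 2/20 have it in set 1 and 6/16 in set 2, where two of the six are the same TEAE returning in the same people.

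Both show 6/20 = 30% of participants and six cases. By set, A goes from 30% to 0% and B from 10% to 37.5%. If the two repeats in B were different TEAEs, or if the event count ignored the single-case rule, the counts would be 8 against 6. Even then nothing would show in which set the events fell.

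**5. Size of the dilution.** Assume all randomized participants form the denominator and all dropout falls before set 2. The apparent set-2 risk is then the true risk × (1 − d). For a true risk of 25%:

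| Dropout | Entering set 2 (of 20) | Apparent risk | Factor |
|---|---|---|---|
| 10% | 18 | 22.5% | 0.9 |
| 20% (planned) | 16 | 20.0% | 0.8 |
| 30% | 14 | 17.5% | 0.7 |

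Losses during set 2 weaken the effect, and with no loss before set 2 there is none.

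**6. What by-set tables can support.** With zero events the one-sided 95% upper bound is 1 − 0.05^(1/n): 13.9% for n = 20 and 17.1% for n = 16. With 16 pairs, an exact McNemar test of 5% against 40% discordance has about 42% power. By-set results can describe but not test.

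**The case against.** The strongest reply is that the article only omits a table. Tabulation by period and the definition of denominators often sit in a full protocol or analysis plan that is not shown. Section 2.9.1 also provides event counts and device-related and serious categories, and it does not exclude a breakdown by set. This stands as far as the missing table goes. It does not cover the single-case and worst-grade rules, which are printed and act across the whole trial. A by-set table built on them would still lose recurrence and worsening.

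A reader might infer that the trial will be unable to say whether harm accumulates. The documents do not support that. Adverse events are scanned in both sets and related TEAEs are identified at every session, so set of first onset should be derivable. One caution remains: if only the worst grade is literally recorded, earlier milder episodes may not be recoverable.

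Other points on that side also stand:

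- Keeping all treated participants in the denominator is ordinary safety practice.
- A rate limited to those who received both sets leaves out anyone who stopped because of harm, and so can understate risk.
- No arm receives 30 unbroken sessions, so no table can show whether the split itself helped.
- The article describes two 15-session sets with a rest throughout and does not claim evidence on an uninterrupted course.

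**Conclusion.** The point holds for the planned summary, not for the data. As written, section 2.9.1 cannot separate harm that fades after set 1 from harm that recurs, worsens or first appears in set 2, although the Discussion gives unreported electrode safety as the reason for having two sets. The 44.8% example rests on assumed risks and on 20% stopping between sets. The ambiguity itself remains without any dropout.

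Dilution is secondary. It is at most a factor of 0.8 at the planned 20% dropout, and that needs two assumptions the article does not state: all randomized participants in the denominator, and all dropout before set 2.

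Two stronger readings should be avoided. The electrode is not without any safety record: the article says unreported in mild cognitive impairment and cites one single-session study of similarly small electrodes in healthy volunteers, though it concedes that no study directly supports the chosen type. Nor do the earlier 20-day studies serve as a benchmark, because the Discussion says they used wider electrodes.

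This is a worthwhile, low-cost correction to the reporting rules and does not invalidate the design.

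**What to change.** In section 2.9.1:

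- Keep the all-treated, whole-trial table as the main safety summary, and state its denominator.
- Add TEAEs and ADEs by arm and by set of onset: set 1, rest, set 2. For each set, the denominator is the participants who received at least one session in it. State the denominator used for the rest interval.
- Apply the once-per-person and maximum-severity rules within each set, and retain every episode in the record.
- Show sessions delivered and discontinuations related to adverse events, by arm and set.
- Label the by-set results descriptive, and note that those entering set 2 are a selected group who tolerated set 1. Do not use a rate among both-set participants as the headline figure.

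This needs no new visits or assessments, since the scan is already scheduled in both sets. The cost is a few extra tables, and smaller denominators with wider intervals for set 2.

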**Discussion:**

For the present study, we hypothesize that compared to a sham group, the optimized personalized tDCS application would be effective in improving the cognitive function of patients with AD-induced MCI and the participants would tolerate the tDCS intervention without any significant adverse effects.

**Clinical trial registration**: https://cris.nih.go.kr, identifier [KCT0008918].

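### The only between-group safety inference is a test of difference, and with 16 to 20 per arm a non-significant result cannot support the statement that safety relative to sham will be proved or validated

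*Protocol article*

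**What the plan says.** Safety is one of the trial's stated aims (Introduction, second specific aim). The abstract gives the hypothesis as an absence of harm: "the participants would tolerate the tDCS intervention without any significant adverse effects". Section 4 (Discussion) goes further. Its opening says that the trial aims to prove feasibility and safety, and its limitations paragraph says that "this study will be able to validate its efficacy and safety relative to sham tDCS".

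Section 2.9.1 sets out the analysis. The descriptive part comes first: "The number of subjects with TEAEs, number of events and percentage per events will be registered", organised into adverse device events, serious adverse events and serious adverse device events. A test is then added: "the differences between groups will be tested using the Pearson’s chi-square test". A bracketed exception replaces it when counts are small, and its condition (the 20 is a percentage) reads "or Fisher’s exact test if the expected frequency is less than five cells and exceeds 20". Occurrences by MedDRA class and preferred term are reported for each group.

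On size, section 2.7 reports no formal calculation: "we decided to recruit a minimum of 32 participants", and after allowing for dropout "the projected number of participants to be recruited will be 40". Section 2.3.4 fixes 1:1 allocation.

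**The concern.** The safety claim and the safety method do not match. The claim is that harm relative to sham is absent, or small enough to call the treatment safe. The method tests whether the arms differ. A significant result would be evidence of harm, but a non-significant one is compatible both with no harm and with a large excess that the trial was too small to detect. Section 2.9.1 names no interval for the between-arm comparison, although section 2.8 specifies a 95% interval for the least squares means.

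This matters more than usual because section 4 itself concedes that the safety of this electrode size has not been reported in an MCI population, and that no earlier study directly supports the electrode type. Device safety is an open question that the trial is meant to inform before a full-scale study. A statement of validated safety that rested on this test would claim more than the data can show.

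**Working it through.** **1. The plan's own figure.** Minimum 32 participants, "Considering a 20% dropout rate": 32 / (1 - 0.20) = 40. The recruitment target reproduces. With 1:1 allocation this is 20 per arm, or 16 per arm if the planned dropout occurs and only completers are counted.

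**2. Inputs that the article does not give.** The significance level and sidedness of the safety test are not stated; two-sided 5% is assumed. No event rates are stated; sham rates of 5% to 20%, with active three times as high, are assumed to show a range. The switch rule is worded unclearly and is read in the conventional way: Fisher's exact test if more than 20% of cells have an expected count below 5, otherwise uncorrected Pearson chi-square.

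**3. Power for a threefold excess.** Let A and S be the numbers of participants with an event in the active and sham arms, independent binomials with n per arm. Power is the sum of P(A = a) × P(S = s) over all tables (a, s) for which the applicable test gives p ≤ 0.05. Exact enumeration gives:

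| Sham vs active | Switch rule, n = 20 | Switch rule, n = 16 | Fisher only, n = 20 | Fisher only, n = 16 |
|---|---|---|---|---|
| 5% vs 15% | 7% | 4% | 7% | 4% |
| 10% vs 30% | 29% | 18% | 24% | 17% |
| 15% vs 45% | 56% | 40% | 44% | 31% |
| 20% vs 60% | 75% | 65% | 65% | 51% |

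Under the switch rule at 20 per arm, the chance of missing a true threefold excess therefore runs from 93% (5% vs 15%) through 71% (10% vs 30%) to 25% (20% vs 60%).

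**4. What a non-significant result leaves open.** Take 6/20 active vs 2/20 sham. The expected event count is 4 in each arm, so two of the four cells are below 5 and Fisher applies: p = 0.24. The Wilson 95% limits are 0.145 to 0.519 for 6/20 and 0.028 to 0.301 for 2/20. Newcombe's interval for the difference of 0.20 is then:

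- lower: 0.20 - √[(0.300 - 0.145)² + (0.301 - 0.100)²] = -0.05
- upper: 0.20 + √[(0.519 - 0.300)² + (0.100 - 0.028)²] = +0.43

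The test finds no difference, while the data remain compatible with an excess of up to 43 percentage points. Even 4/20 vs 0/20 is non-significant (Fisher p = 0.11); it takes 5/20 vs 0/20 to reach p = 0.047.

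**5. No events at all.** The exact two-sided 95% upper limit for zero events is 1 - 0.025^(1/n): 1 - 0.025^(1/20) = 16.8% and 1 - 0.025^(1/16) = 20.6%. An arm with no serious device event would still not exclude a rate of about one in six.

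**The case against.** A reader might infer that the plan would treat a non-significant p-value as proof of safety. The article does not say so. No section ties the safety conclusion to the test. The test is an addition to counts and percentages by group, and section 2.9 also lists vital signs, physical examinations and monitoring of concomitant medication. The sentence about validating safety names no test or threshold. In the hypothesis, *significant* adverse effects most naturally means clinically important ones. All of this stands.

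A reader might also infer that the test misses a threefold excess about three times in four as a general property. That holds only near 10% vs 30% at 20 per arm with Fisher's test (76% missed; 71% under the switch rule). The article states no event rate, and if events are common the test does considerably better.

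Finally, the choice of interval for adverse event tables is often left to an analysis plan, the intervals could be computed from the planned counts, and this is openly a feasibility study without a power calculation. That disposes of any complaint about missing detail. It does not remove the mismatch: the article states a method, states a conclusion in strong terms, and the one cannot deliver the other. Feasibility status argues for estimates with their uncertainty rather than for a test.

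**Conclusion.** The point holds in a limited form. The only between-group safety inference described is a test of difference, while section 4 says that safety will be proved, and validated relative to sham. With 20 per arm (16 after dropout) a non-significant result cannot support that statement. The size of the problem depends on event rates that the article does not give. Under the assumed two-sided 5% level and conventional switch rule, power for a threefold excess is at most 29% when the sham rate is 10% or lower, and reaches 75% at 20% vs 60% with 20 per arm. For rare categories, which serious device events may well be, the test is close to uninformative. The argument about what a non-significant test can show does not depend on these assumed rates. The documents do not support the further claim that the investigators have committed to reading non-significance as safety. This is a point that should be corrected, not one that undermines the trial.

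**What to change.** Keep the planned counts and percentages. Base the safety statement on the between-arm risk difference with a 95% confidence interval (for example Newcombe's) for any treatment-emergent event, any adverse device event and the common preferred terms, with exact (Clopper-Pearson) intervals for each arm, instead of on the p-value. In section 4, replace the wording about proving and validating safety with a statement of the event rates and rate differences that the upper confidence limits exclude.

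No new data, visits or participants are needed. The cost is one more table column, some rewording and a less favourable safety claim.
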